## Method

### Design

The study is a 2 (Baby Triple P vs CAU) × 3 (time: pre-test, post-test, 6-month-follow up) design with multi-informant assessment. The study will experimentally test the relative impact of Baby Triple P against care as usual in a randomized controlled trial aimed at improving baby and parenting outcomes. The CONSORT guidelines for randomized controlled trials will be used. This protocol also adheres to the SPIRIT guidelines.

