### Primary analyses

The analyses will evaluate the effects of the intervention on parent and baby outcomes, including the primary outcome measures of parenting confidence and sense of competency. These analyses will include self-reports obtained from parents as well as reports on baby behaviors, baby diaries and observational assessment. A multilevel modeling approach will be used to take into account the repeated measurements and thus non-independence of observations [84]. This approach will be used for variables that have three measurement time points (e.g. Couple Relationship and the EPDS). Dummy codes contrasting the groups will serve as fixed effects, allowing for random intercepts and slopes to vary across individuals. Outcome variables with two time points (e.g., MSES, and the Baby Diary) will be analyzed using a series of rANOVAs and rMANOVAs. The primary analyses will be conducted for mother and father data separately to investigate whether the intervention is beneficial for both parents, or has different effects for mothers and fathers. Significant fixed effects contrasting Baby Triple P with CAU will indicate whether the intervention is an improvement over usual care. Separate models will be estimated for each outcome measure using Bonferroni correction to control for inflation of Type 1 error due to multiple comparisons.

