### Sample size and power analysis

The required sample size for the study was calculated to assure 80% power to detect a medium effect size (ES) = 0.5 for a mean difference in the variables of interest between the groups (INT vs CAU). Effect sizes for early intervention studies range from small to large on a range of outcomes [48]. Two studies that assessed parental confidence and competence as an outcome of a parenting intervention found a small [85] and a large [43] effect. Given these are our primary outcome measures, a medium effect size was expected in this study. Furthermore, as our study will recruit an at-risk sample, an expected medium effect is a conservative estimate. We performed power analysis using G*Power software [86] for rANOVA, looking at the within-between interactions and allowing for conservative estimate of intra-individual variability (.5). The analyses indicated that a sample size of 80 is sufficient to detect an ES of 0.5 at the significance level of .05 (two-tailed). This is without taking into account the added power accorded by the rich repeated measures in our data. In multilevel models with repeated measures, the sample size is effectively the number of observations (level-1), not number of participants (level-2 units). Assuming a 20% attrition rate (based on estimate within Bakermans-Kranenburg, van Ijzendoorn [46] review), an available sample of 110 families will be sufficient to detect medium sized effects.

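### The 80% power is stated at alpha .05, but the primary outcomes will be tested with a Bonferroni correction that the power statement ignores

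*Protocol article*

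**What the plan says.** Sample size and power analysis says that the sample size was "calculated to assure 80% power to detect a medium effect size (ES) = 0.5 for a mean difference" between the arms. It ties the choice of a medium effect to confidence and competence because these are the primary outcomes. The calculation was done "for rANOVA, looking at the within-between interactions and allowing for conservative estimate of intra-individual variability (.5"), and the result is given as: "The analyses indicated that a sample size of 80 is sufficient to detect an ES of 0.5 at the significance level of .05 (two-tailed"). Enrolment of 110 families allows for 20% attrition. No multiplicity adjustment appears in that section.

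Primary analyses covers all parent and baby outcomes and expressly includes the two primary measures. It adds: "The primary analyses will be conducted for mother and father data separately". It ends: "Separate models will be estimated for each outcome measure using Bonferroni correction to control for inflation of Type 1 error due to multiple comparisons". It does not give the number of comparisons, does not exempt the primary outcomes, and does not separate them from the secondary ones.

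Table 1 lists the confidence inventory at T1, T2 and T3, and the self-efficacy measure at T2 and T3 only.

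**The concern.** The sample size section and the analysis section use different significance levels for the same hypotheses. The stated 80% belongs to a test at .05. The test that will be made uses .05 divided by some number of comparisons, and that number is at least two because there are two primary measures.

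Two things are at stake. First, the power claim does not describe the planned test. Second, if the correction is read across every outcome measure, ten secondary instruments use up most of the alpha of the two outcomes the trial was sized for. A null primary result would then be hard to interpret. The Background section already attributes earlier null trials of this programme partly to small samples, so the question matters here.

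**Working it through.** **Inputs from the protocol article.** Two arms and three times (Design); effect size 0.5, two-tailed .05, 80% power, N = 80, 110 families, 20% attrition (Sample size and power analysis). Completers: 110 × 0.8 = 88.

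**Assumptions.** Equal allocation, since no ratio is given. The 0.5 is a standardised mean difference, so Cohen's f = 0.5 / 2 = 0.25.

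**Reproducing the stated N.** For the within-between interaction with m times and N participants:

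- noncentrality λ = f² × N × (m − 1)
- degrees of freedom (m − 1) and (N − 2)(m − 1)
- power = probability that a noncentral F exceeds the critical F at alpha

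With m = 3 and N = 80: λ = 0.0625 × 80 × 2 = 10, df = 2 and 156, critical F = 3.05, power = .807. N = 80 is reproduced. With 20% attrition, 80 / 0.8 = 100, so 110 families leave some margin.

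This match is not unique. The formula does not use the stated .5 for intra-individual variability, and the article does not name the software option.

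**Counting tests.**

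- Two primary measures: 2 tests, alpha .05 / 2 = .025.
- Two primary measures in each parent: 4 tests, alpha .0125.
- All Table 1 instruments that can be compared between arms after birth: confidence, self-efficacy, depression, anxiety/stress, worry, happiness, couple relationship, responsiveness, observed interaction, bonding, baby behaviour, diary. That is 12 tests, alpha .0042.
- The same 12 plus the fathers' 9 (no worry scale, no observation, one diary per couple): 21 tests, alpha .0024.

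**Power at 88 completers, three times.** λ = 0.0625 × 88 × 2 = 11, df = 2 and 172.

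| Tests | Alpha | Critical F | Power, N = 88 | Analysed N for 80% | Enrolled (÷ 0.8) |
|---|---|---|---|---|---|
| 1 | .05 | 3.05 | .846 | 80 | 100 |
| 2 | .025 | 3.77 | .769 | 94 | 118 |
| 4 | .0125 | 4.50 | .684 | 110 | 138 |
| 12 | .0042 | 5.66 | .543 | 132 | 165 |
| 21 | .0024 | 6.26 | .474 | 144 | 180 |

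The margin from 80 to 88 does not absorb even the smallest correction.

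**Self-efficacy, two times.** λ = 0.0625 × 88 × 1 = 5.5, df = 1 and 86. Power is .640 at .05, .528 at .025 and .423 at .0125.

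**Sensitivity for self-efficacy.** If the tested contrast were instead the difference between arms averaged over T2 and T3, with an assumed correlation of .5 between visits, power at 88 would be .764, .665 and .564. That is also below 80% at each alpha.

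**The case against.** The strongest objection is that the family is not defined. A reader might infer that primary and secondary outcomes certainly share one correction over 12 or 21 tests, so that the primaries are tested at a far smaller alpha than planned. The text permits that reading but does not establish it. It gives no divisor, and the family could be the two primaries, the outcomes within a domain, or each parent's set. The count itself is soft. The planned rMANOVAs could bundle measures and lower it, while subscales of the anxiety/stress, bonding and observation measures could raise it. This objection stands. What survives it is the upper bound: with two primary measures, alpha is at most .025.

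A reader might also measure the loss with a single-visit comparison at 88 completers. Power is then 64% unadjusted, or 76% adjusted for baseline with an assumed correlation of .5, before any correction. Those figures mix in a different problem, because the plan powers a repeated-measures interaction. The baseline-adjusted figure cannot apply to self-efficacy, which is not measured at baseline. The loss due to the correction is better read from the formula that reproduces N = 80.

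Third, another form of the interaction calculation uses a correlation of .5 (λ = N f² m / (1 − .5)). It would keep power at 80 participants at about .90 or more even with 21 tests. But it needs only 28 participants (three times) or 34 (two times) for 80% power at .05, so it does not explain the stated 80, and the article claims no such reserve. Its remark on added power from repeated measures is not quantified.

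Finally, an overly wide Bonferroni family is conservative. It neither biases the estimates nor raises the false-positive rate. That is true, and it limits the harm to lost power and an inaccurate power statement.

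**Conclusion.** The mismatch is real on any reading of the family. The trial is sized at .05, while the primary outcomes are tested at .025 or less. Under the formula that reproduces the stated 80, power at 88 completers falls from 85% to 77% when the family is the two primaries, and to 68% when both parents count. It would be 54% or 47% if all 12 instruments, or all 21 tests, share one correction; those two figures are conditional on a reading that the article neither confirms nor excludes. Self-efficacy is weaker throughout under the same formula: 64% at .05, 53% at .025 and 42% at .0125.

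These sizes rest on f = 0.25, equal arms, the 20% attrition assumption and an interaction formula inferred from the stated N. That the stated power does not carry over to the corrected test does not depend on which divisor is chosen. The exact shortfall does.

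**What to change.** 1. Define the confirmatory family as the two primary measures, or as the two measures in each parent if both parents are confirmatory (four tests).
2. Correct within that family only. Holm controls the same familywise error as Bonferroni and never rejects fewer hypotheses. Keeping Bonferroni is also valid.
3. Put the secondary outcomes in a separate family, or report them as supportive.
4. Restate power for 88 completers at the alpha actually used, separately for confidence (three visits) and self-efficacy (two visits), and name the software option.

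The Discussion says that recruitment closed in March 2015 and follow-up ended in January 2016, with analyses still to be completed. Enrolment can no longer change. Narrowing a published correction at this stage is defensible only if it is decided and recorded with a date before outcomes are seen by arm. Beyond that record, the cost is a few sentences of analysis wording. The small downside is that secondary outcomes lose confirmatory status and the stated power falls.

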**Methods/design:**

Participants will be randomized to either Group Baby Triple P or Care as Usual (CAU). Group Baby Triple P involves 4 × 2 h group sessions delivered during pregnancy and 4 individual telephone sessions of 30 min each in the early postnatal period. Outcomes will be assessed via parent self-report questionnaire, home observations and a baby diary 10 weeks and 6 months post-birth. Primary outcomes will be parental confidence and perceived competence. Secondary outcomes will include parental responsiveness and bonding with the baby, relationship happiness, life satisfaction, depression, anxiety and stress, and infant crying and sleep. Analyses will involve a series of rANOVA and rMANOVAs, t-tests and a multilevel modeling approach.

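### The plan fixes plain Bonferroni; Holm's step-down procedure would hold the same family-wise error, never reject less, and gain power when more than one effect is real

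*Protocol article*

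**What the plan says.** The Primary analyses section states: "Separate models will be estimated for each outcome measure using Bonferroni correction to control for inflation of Type 1 error due to multiple comparisons". No step-down version is named, so the ordinary reading is that every test in the family is judged at .05/m. The number of tests m and the adjusted level are not stated.

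The abstract says "Primary outcomes will be parental confidence and perceived competence". The Primary analyses section adds: "The primary analyses will be conducted for mother and father data separately". The stated reason is to see whether the intervention helps both parents or affects them differently. The Aims and hypotheses section expects benefit on both primary constructs and on a list of secondary ones.

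The Sample size and power analysis section aims for "80% power to detect a medium effect size (ES) = 0.5 for a mean difference in the variables of interest between the groups". It sizes "for rANOVA, looking at the within-between interactions" and works "at the significance level of .05 (two-tailed"). No multiplicity adjustment appears in that calculation.

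**The concern.** Bonferroni and Holm give the same guarantee: the chance of any false rejection in the family is at most .05, whatever the dependence between outcomes. They differ once one hypothesis has been rejected. Bonferroni keeps the .05/m threshold for the rest, whereas Holm relaxes it step by step.

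That difference bears on the questions this trial asks. Whether the programme improves both confidence and competence, and whether it helps both mothers and fathers, can be answered positively only by a second or later rejection. The article also attributes earlier null results for this programme partly to small samples, and it sizes the present trial at an unadjusted .05, so there is no stated reserve to absorb the correction.

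**Working it through.** **The plan's own figures.** The plan states no number for the Bonferroni step, so there is none to reproduce. The nearest figure is the sample size of 80 for 80% power. A repeated-measures interaction with f = 0.25, three time points and noncentrality f² × N × (time points − 1) = 0.0625 × 80 × 2 = 10 gives 80.7% power at N = 80. That version has no place for the stated .5 for intra-individual variability; the other forms tried do not give 80. Attrition is covered: 80/0.8 = 100, and 110 × 0.8 = 88. For this point I take the plan's 80% power at .05 at face value.

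**Inputs**
- Overall level .05 two-sided and 80% power per real effect: Sample size and power analysis.
- Two primary outcomes: abstract. Mothers and fathers separately: Primary analyses.
- Family size m: not stated. Assumed m = 2 (two primaries, one parent), m = 4 (2 × 2), and m = 20 (roughly all outcomes).
- Correlation between test statistics: not stated. Assumed 0 to .5.
- Number of real effects: not known. Varied.

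**Procedures.** Bonferroni rejects if p ≤ .05/m. Holm orders the p-values and rejects the j-th smallest while it is ≤ .05/(m − j + 1). For m = 4 the Holm thresholds are .0125, .0167, .025 and .05.

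**Why Holm never loses.** Since .05/(m − j + 1) ≥ .05/m, anything that passes Bonferroni passes Holm. With m₀ true nulls, at least m₀ hypotheses remain when the first true null is reached, so its threshold is at most .05/m₀. The chance that any true null falls below that is at most m₀ × .05/m₀ = .05, with no assumption on dependence. The first steps are identical, so the chance of at least one rejection is identical.

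**Bonferroni power.** 80% power at .05 corresponds to a mean test statistic of 1.960 + 0.842 = 2.802.
- m = 2: Φ(2.802 − 2.241) = 71.2%
- m = 4: Φ(2.802 − 2.498) = 61.9%
- m = 20: Φ(2.802 − 3.023) = 41.2%

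**Holm, m = 2, both effects real, independent tests.** Let a = .712 (power at .025) and b = .800 (power at .05).
- Per test: a + (b − a) × a = .712 + .088 × .712 = 77.5%
- Both rejected: b² − (b − a)² = .640 − .008 = 63.2%, against a² = 50.7% with Bonferroni
- At least one: 1 − (1 − a)² = 91.7% for both procedures
- Only one effect real: a + (b − a) × .025 = 71.5%, against 71.2%

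**Simulation** (200,000 to 400,000 replicates per scenario), power per real effect:

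| Family | Real effects | Correlation | Bonferroni | Holm |
|---|---|---|---|---|
| 2 | 2 | 0 | 71% | 77.5% |
| 2 | 2 | .5 | 71% | 76.5% |
| 4 | 4 | 0 | 62% | 72.7% |
| 4 | 4 | .5 | 62% | 71.0% |
| 4 | 2 | 0 | 62% | 64.4% |
| 4 | 2 | .5 | 62% | 64.2% |
| 4 | 1 | 0 to .5 | 62% | 62% |
| 20 | 20 | 0 | 41.2% | 49.4% |
| 20 | 10 | 0 | 41.2% | 43.9% |
| 20 | 1 | 0 | 41.4% | 41.5% |

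With all nulls true the two procedures have identical family-wise error (for m = 4, 4.9% at correlation 0 and 4.3% at .5). No replicate showed a Bonferroni rejection that Holm missed.

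**Sensitivity.** If each test is instead a simple two-group comparison at d = 0.5 with 80 in total (60.9% power at .05), then for m = 4 and correlation .5 power per real effect goes from about 40% to 47% with four real effects, from 40% to 41% with two, and is unchanged with one.

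**The case against.** The strongest reply is that nothing here is wrong. Bonferroni is prespecified, standard and controls the error it is meant to control; nothing in the article contradicts it, and the same remark could be made of any trial that uses it. That stands, and the point should be read as an improvement only.

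Several stronger readings are tempting and should not be drawn:
- *Holm has higher power in every family.* It does not. The chance of at least one rejection is the same, and with a single real effect the gain is about zero. The plan states no rule that both primaries must succeed, so the gain in both being rejected is not a gain on a stated success criterion.
- *Power is given away for nothing.* Bonferroni offers one fixed threshold and matching simultaneous intervals. Holm's intervals are less simple, and an unadjusted 95% interval can exclude zero while the Holm-adjusted p-value exceeds .05.
- *Positively related scales are where the loss is largest.* For families of two and four with all effects real, the gain shrinks slightly as correlation rises (about 6 to 5 points, and 11 to 9). The number of real effects drives it.
- *Holm repairs the mismatch with the sample size section.* It does not, because its first step still uses .05/m while the trial was sized at an unadjusted .05.

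Two further objections do not defeat the point. The family is not stated, but Holm applies to whatever family Bonferroni would have used, and its dominance holds for any m; only the size of the gain depends on it. Follow-up is already complete according to the Discussion, so a change to a procedure that can only reject more could look like a post hoc relaxation. That is met by dating the change before any group results are seen.

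**Conclusion.** The point holds as an efficiency improvement. Holm keeps the .05 family-wise guarantee and never loses a Bonferroni rejection; both facts are free of assumptions. The size of the gain rests on assumed values: 80% unadjusted power per real effect, families of two or four, and correlations of 0 to .5. On those, the gain per test is about 5-6 points (m = 2) or 9-11 points (m = 4) if all effects are real, 2-3 points if two of four are, and about zero if one is. The all-real case is what the trial hypothesises, but the earlier trials of this programme that the article describes found no significant effects, so the smaller gains are equally plausible.

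**What to change.** In the Primary analyses section, replace the Bonferroni correction with Holm's step-down procedure at family-wise .05, applied to the same family that Bonferroni would have covered. Record and date the change before anyone sees results by group; if they have already been seen, keep Bonferroni. Report Holm-adjusted p-values, and label 95% confidence intervals as unadjusted.

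The cost is one phrase and a dated note, with no new data. The drawback is that simultaneous intervals matching the tests are less simple than under Bonferroni. The unadjusted .05 in the Sample size and power analysis section is untouched by this change and needs its own statement.

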### Sample size and power analysis

The required sample size for the study was calculated to assure 80% power to detect a medium effect size (ES) = 0.5 for a mean difference in the variables of interest between the groups (INT vs CAU). Effect sizes for early intervention studies range from small to large on a range of outcomes [48]. Two studies that assessed parental confidence and competence as an outcome of a parenting intervention found a small [85] and a large [43] effect. Given these are our primary outcome measures, a medium effect size was expected in this study. Furthermore, as our study will recruit an at-risk sample, an expected medium effect is a conservative estimate. We performed power analysis using G*Power software [86] for rANOVA, looking at the within-between interactions and allowing for conservative estimate of intra-individual variability (.5). The analyses indicated that a sample size of 80 is sufficient to detect an ES of 0.5 at the significance level of .05 (two-tailed). This is without taking into account the added power accorded by the rich repeated measures in our data. In multilevel models with repeated measures, the sample size is effectively the number of observations (level-1), not number of participants (level-2 units). Assuming a 20% attrition rate (based on estimate within Bakermans-Kranenburg, van Ijzendoorn [46] review), an available sample of 110 families will be sufficient to detect medium sized effects.

### Missing outcome data

The full information maximum likelihood analysis (FIML) approach will be implemented to accommodate for missing data when using a multilevel modeling approach. For other variables analyzed using rANOVA and rMANOA, multiple imputations will be used. If the assumptions of either Missing Completely at Random (MCAR) or Missing at Random (MAR) are met [87], then these approaches will yield estimates consistent with what would be expected if there were no missing data. Thus, it will allow intention-to-treat analysis (inclusion of all randomized families in the analyses).

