#### Additional variables

*Parent Attendance* will be assessed by the group facilitator taking attendance of both mothers and fathers at the group sessions. This will only be assessed for parents in the intervention group. It will be coded as either present or not present for both mothers and fathers.

The *Conflicting Advice Questionnaire* and *Problem Solving* is a 6­item measure that was developed for this study to assess the extent participants received conflicting information or advice from professionals and from family and friends, as well as how they deal with confusion and problems. First, it asks about the extent of confusion in regards to five areas, separately from professionals, and from friends and family: feeding the baby, settling the baby, putting the baby to sleep, bathing the baby and dressing and changing the baby. Then, participants are asked to write about any other topics where they experience confusion. Next, participants are asked about what they do when they are confused or encounter a problem in regards to their baby. They can tick one or more of the following options: seek out additional information from family, seek out additional information from professionals, research the internet, corroborate with partner about the problem and try to think of a solution together, try out different strategies until one works. The final item allows participants to write about any other problem solving strategies they have been using.

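### The intention-to-treat claim rests on missing at random given arm and observed outcomes, with no stated role for recorded attendance, so the estimate may be modestly too favourable

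*Protocol article*

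**What the plan says.** All references are to the protocol article.

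- **Missing outcome data**, outcomes with three time points: "The full information maximum likelihood analysis (FIML) approach will be implemented to accommodate for missing data when using a multilevel modeling approach".
- **Same section**, outcomes with two time points: "For other variables analyzed using rANOVA and rMANOA, multiple imputations will be used". The variables in the imputation model are not listed.
- **Same section**, the condition attached to both methods: "If the assumptions of either Missing Completely at Random (MCAR) or Missing at Random (MAR) are met". The conclusion drawn from that condition: "Thus, it will allow intention-to-treat analysis (inclusion of all randomized families in the analyses".
- **Primary analyses**, the multilevel model: "Dummy codes contrasting the groups will serve as fixed effects, allowing for random intercepts and slopes to vary across individuals". Table 1 gives the primary confidence measure three time points, so it falls under this model. The primary self-efficacy scale is measured only at T2 and T3, so it goes to repeated-measures ANOVA with multiple imputation.
- **Additional variables**: attendance "will be assessed by the group facilitator taking attendance of both mothers and fathers at the group sessions". On scope: "This will only be assessed for parents in the intervention group".
- **Discussion**: the authors cite research that intervention effects are larger if mother and father both take part.

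None of the paragraphs under Statistical analyses mentions attendance.

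**The concern.** An analysis that includes every randomised family through FIML or imputation fills in the lost families from a model. Whether the result estimates the effect over all randomised families depends on what that model conditions on.

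There are three reasons to doubt that arm and observed outcomes are enough here.

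1. The intervention is an eight-session programme. It is plausible, though not stated, that a family that stops coming is also less likely to return questionnaires.
2. The Discussion makes it plausible that benefit varies with attendance, although its remark concerns both parents taking part rather than the number of sessions.
3. A family lost before T2 has only T1 data, collected before randomisation. Those data say nothing directly about how much of the programme the family received. On the self-efficacy scale such a family has no score of its own.

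If the first two hold, lost families in the intervention arm benefited less on average than retained families of that arm, and a model without attendance cannot see it. Programme attendance exists in one arm only, so this mechanism would not cancel in the comparison. The primary outcomes are affected. The variable that could reduce the problem has already been collected.

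**Working it through.** **The plan's own figure.** The article gives no figure for this bias. The nearest is attrition: 20% loss from 110 families leaves 110 × 0.8 = 88, which covers the 80 required. That arithmetic is not in dispute here.

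**Illustration.** The splits below are assumptions; the article gives none of them. Only the 0.5 SD effect and the approximate 20% loss echo its planning values. Loss under care as usual is taken as ignorable.

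- Attenders: share 0.70, effect 0.5 SD, retained 0.90.
- Stoppers: share 0.30, effect 0, retained 0.50.
- Retained attenders: 0.70 × 0.90 = 0.63. Retained stoppers: 0.30 × 0.50 = 0.15. Total 0.78, a loss of 22%.
- Effect over all randomised families: 0.70 × 0.5 + 0.30 × 0 = 0.35 SD.
- MAR given arm, without attendance: lost families take the average of retained families, 0.5 × 0.63 / 0.78 = 0.404 SD.
- Excess: 0.404 − 0.35 = 0.054 SD; ratio 0.404 / 0.35 = 1.15.
- MAR given arm and attendance: each level is filled in from its own level, which returns 0.35 SD if MAR holds within level.

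**Varying the retention of stoppers**, all else fixed:

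| Stoppers retained | Total retained | Estimate (SD) | Excess (SD) |
|---|---|---|---|
| 90% | 0.63 + 0.27 = 0.90 | 0.5 × 0.63/0.90 = 0.350 | 0 |
| 70% | 0.63 + 0.21 = 0.84 | 0.5 × 0.63/0.84 = 0.375 | 0.025 |
| 50% | 0.63 + 0.15 = 0.78 | 0.404 | 0.054 |
| 30% | 0.63 + 0.09 = 0.72 | 0.5 × 0.63/0.72 = 0.438 | 0.088 |

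The excess is also zero if attenders and stoppers benefit equally.

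**Outer range.** If retained intervention families benefit by 0.5 SD on average, the excess is (share lost) × (share of the lost without benefit) × 0.5. At 20% loss it runs from 0 to 0.20 × 1 × 0.5 = 0.10 SD; at 10% loss from 0 to 0.05 SD; at 30% loss from 0 to 0.15 SD.

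**Simulation with other assumed inputs.** With 25% non-attenders, 60% of them lost against 6.7% of attenders, overall loss is 0.25 × 0.60 + 0.75 × 0.067 = 0.20. The true mean effect was 0.376 SD. MAR given arm gave 0.437 without a baseline score and 0.440 with one correlated 0.5 with the outcome. Adding attendance gave 0.373 to 0.377. The baseline did not help because it was generated independently of attendance. A baseline that predicts attendance would recover part of the difference.

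**Scale.** With 88 retained families in two equal arms, the standard error of a simple mean difference is about 2/√88 = 0.21 SD. An excess of 0.054 SD is about a quarter of that.

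**The case against.** The strongest reply is that the article does not say attendance will be left out. It lists no imputation variables, and such detail is commonly left to a statistical analysis plan, which is not shown here. This stands for the two-time-point outcomes, including self-efficacy: a reader might infer that attendance is excluded there, but all that can be said is that it has no stated role. It carries less weight for the confidence measure, because the multilevel model's fixed effects are described and attendance is not among them.

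Other parts of the reply also stand.

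- MAR is stated as a condition, not a fact, and the conditional sentence is correct as written.
- A reader might infer that families who stop attending are treated as missing. They are not. Assessments fall at fixed times in both arms, and a non-attender who is assessed counts with their own data.
- A reader might infer that lost non-attenders are credited with the full benefit of attenders. The arithmetic does not support that: they receive the average of all retained families (0.40 SD in the illustration, not 0.50 SD), because retained stoppers are part of that average.
- A family lost before T2 still has T1 scores on confidence, mood, happiness and the couple relationship, which an imputation model could use.

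What the reply does not repair is the step from MAR, with no conditioning set given, to an intention-to-treat claim in a trial that records an obvious predictor of loss and names no use for it.

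**Conclusion.** The point holds in a limited form. The intention-to-treat claim depends on MAR given arm and observed outcomes for the outcomes analysed by the multilevel model, and on an unstated conditioning set for the imputed ones. Attendance has no stated role in either.

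An estimate that is too favourable is possible, not shown. It needs loss to depend on attendance and benefit to depend on attendance, both after allowing for the observed data, with ignorable loss under care as usual. Under the illustrative splits the excess is about 0.05 SD, small against the standard error. It could approach 0.10 SD at 20% loss if none of the lost families benefited, and it is zero if either dependence is absent. The documents do not support a statement that the planned estimate is biased or that the intention-to-treat label is false. The change is still worth making: it is cheap, concerns the primary outcomes and uses data already in hand.

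**What to change.** In the Missing outcome data section:

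1. For two-time-point outcomes, run multiple imputation separately by arm. In the intervention arm, include the number of group sessions attended by that parent as an auxiliary variable.
2. For three-time-point outcomes, either bring the same variable into FIML as an auxiliary variable or fit the multilevel models to the same imputed data sets. FIML need not be abandoned. Attendance should not become a covariate in the outcome model, since it arises after randomisation and exists in one arm only.
3. State that the intention-to-treat estimate assumes MAR given arm, observed outcomes and attendance.

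All randomised families stay in the analysis, so this does not turn it into a per-protocol comparison. The article reports that follow-up was complete but analyses were not, so the change was feasible at that stage and needs no new data.

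**Cost.** Wording and one variable; slightly wider intervals and possibly a slightly smaller estimate. The imputation would lean on few retained low attenders. Assuming equal arms of 55, the illustration has 55 × 0.30 × 0.50, about 8 retained stoppers, standing in for about 8 lost ones. It still assumes MAR within attendance level.

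**Limit.** The attendance record covers group sessions only, so stopping during the telephone sessions is not captured. The adherence checklists are completed for sessions conducted and are not said to show which parent took part, and data collection has closed. No extension of the record is therefore proposed.
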